### Exercise intervention

The exercise sessions will take place twice a week (40 sessions in total): once a week a supervised group session is offered and once a week the patient does an individual training, with clear instructions beforehand and an evaluation at the beginning of the next supervised session. Each supervised session, in which the trainers are working according to a standardized protocol, lasts one hour, of which 30 min are spent running (RT)/Nordic walking (NW). The remaining time is spent on warming-up and cooling-down. Each patient follows an individualised intervention protocol with a gradually increasing training intensity. The goal is to achieve a 30 min period of continuous running in the last sessions (two times a week 30 min continuous aerobic exercise at least 60% of the maximal heart rate). The NW program follows a comparable progressive schedule with increased time spent Nordic walking with high intensity.

Intensity in RT as in NW is monitored by the instructor during every supervised session by counting the heart rate and three times during the intervention period by electronic registration (Polar RS 400, Electro Oy, Finland). The control group receives usual care for depression in accordance with the revised Dutch guideline [51] and are advised to exercise regularly. Hospitalised and day-care patients in the control group are supposed not to participate in organised high intensity aerobic exercise during the intervention period. Only low-intensity activity psycho-motor therapy is allowed.

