### Sample size

Following earlier RCTs [34] it is expected that patients in the usual care group (controls) will respond with a mean reduction in HRSD of six points. Adding exercise to usual care is expected to result in a decline of at least eight points in HRSD score (thus two extra points). To detect this difference, with an α (two-tailed) of 5% and a power (1-β) of 80%, using two equal groups and a standard deviation of 5 points, 100 patients are needed in each group. Taking 30% drop-out into account, 140 patients have to be included in each group.

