### Compliance and withdrawal

In order to improve compliance during the intervention period, a protocol will be followed concerning missed exercise therapy sessions by participants. This protocol includes: 1) active approach by the exercise instructor in case of no show, and 2) encouragement of other participants to contact each other in case of no show. Participants can withdraw at any time for any reason without any consequences. Also, the investigator can decide to withdraw a participant from the study for urgent medical reasons. Participants who withdraw from the intervention will be asked the reason(s) for drop-out but will be retained in the study for the intention to treat analysis.

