### Statistical analyses

Comparability of the intervention and control groups will be examined for the baseline measurements. If necessary, analyses will be adjusted for baseline differences. The primary analysis of the data set will be according to the 'intention to treat' principle. A secondary 'per protocol' analysis will be done taking into account the level of compliance and the amount of exercise during the intervention period. Usual daily physical activity, tobacco smoking and alcohol intake will be treated as confounders.

Differences in remission rates (and other categorical outcomes) between the experimental groups are examined by contingency table Chi-square statistics. Differences in mean scores on continuous outcomes (e.g. HRSD) between the intervention groups are examined by analysis-of-variance.

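### Exercise is delivered in groups, but neither the sample size nor the stated HRSD analysis allows for within-group correlation; if that correlation is positive, the standard error is too small and the 80% power too high

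*Protocol article*

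**What the plan says.** **Delivery.** The Abstract calls the programme group-based. The Exercise intervention section gives two weekly sessions: "once a week a supervised group session is offered", and the second is trained individually, instructed in advance and reviewed at the next supervised session. The Compliance and withdrawal section adds an approach by the instructor after a missed session and "encouragement of other participants to contact each other in case of no show". The Exercise part of the Background lists social integration among the benefits of taking part. Controls receive usual care, with no exercise groups run by the trial.

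**Allocation.** Patients are randomised individually, separately at each location (Randomisation, blinding and treatment allocation).

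**Sample size.** For a two-point difference in HRSD reduction (eight against six), two-sided 5% and 80% power, the article states: "using two equal groups and a standard deviation of 5 points, 100 patients are needed in each group". Then: "Taking 30% drop-out into account, 140 patients have to be included in each group". No group size, ICC or design effect appears.

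**Analysis.** Under Statistical analyses, mean scores on continuous outcomes, with HRSD as the example, "are examined by analysis-of-variance". No group or instructor term is stated.

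**The concern.** This is a partially nested design: patients are independent at randomisation, but those in one arm are then treated together. Shared sessions, a shared instructor and encouraged contact after absences are all routes by which outcomes in the exercise arm could become alike within a group. Randomising within location balances differences between locations. It does not deal with correlation that the intervention itself creates after allocation.

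An ordinary analysis of variance and the usual two-sample formula treat all patients as independent. Under positive within-group correlation, the exercise-arm mean varies more than those methods assume. The confidence interval for the HRSD difference would then be too narrow, the test would reject a true null hypothesis more often than 5%, and a valid test would have less than the stated power.

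**Working it through.** **Inputs from the Sample size section.** Difference 2, SD 5, two-sided alpha 5%, power 80%, 100 analysed per arm, 30% drop-out, 140 recruited per arm.

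**Assumed, because the document does not give them.** Group size m = 8 (5 and 12 as checks), ICC 0.01 to 0.05, and total SD 5 in both arms.

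**Step 1: reproduce the plan's figure under independence.**
n = 2 × [5 × (1.960 + 0.842) / 2]² = 2 × 49.07 = 98.1, so 99 per arm by the normal approximation and 100 by the t distribution. The stated 100 is therefore the independent-observations result, with no clustering allowance hidden in it.

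**Step 2: look for reserve.**
- 100 analysed: SE = 5 × √(2/100) = 0.707; power = Φ(2/0.707 − 1.96) = 80.7% (80.4% by t).
- 140 × 0.7 = 98 analysed: SE = 5 × √(2/98) = 0.714; power = Φ(2.80 − 1.96) = 80.0% (79.6% by t).

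At the planned drop-out, any positive ICC takes power below 80%.

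**Step 3: add clustering in the exercise arm only, 100 analysed per arm.**
- Design effect in the exercise arm: DE = 1 + (m − 1) × ICC; controls have DE = 1.
- True SE = 5 × √[(1 + DE)/100].
- Type I error of the planned test = 2 × [1 − Φ(1.96 × 0.707 / true SE)].
- Power of a test that uses the true SE = Φ(2 / true SE − 1.96).
- Chance that the planned test rejects at a true two-point difference = Φ[(2 − 1.96 × 0.7071) / true SE].

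| m = 8 | DE | True SE | True SE / 0.707 | Planned test: type I error | Planned test: rejects at 2 points | Test allowing for clustering: power |
|---|---|---|---|---|---|---|
| ICC 0.01 | 1.07 | 0.719 | 1.017 | 5.4% | 80.3% | 79.4% |
| ICC 0.02 | 1.14 | 0.731 | 1.034 | 5.8% | 79.9% | 78.1% |
| ICC 0.05 | 1.35 | 0.767 | 1.084 | 7.1% | 78.8% | 74.2% |

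The type I error and the final power column belong to different tests. The planned test keeps its rejection rate near 79% to 80% because its type I error exceeds 5%.

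**Step 4: sensitivity to group size, ICC 0.01 to 0.05.**
- m = 5: type I error of the planned test 5.2% to 6.2%; power of the test allowing for clustering 80.0% to 76.9%.
- m = 12: 5.6% to 8.3%; 78.6% to 70.7%.

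**Step 5: size needed for 80% power with equal arms, m = 8.** n = (1 + DE) × 49.06 (unrounded factor).
- ICC 0.01: 2.07 × 49.06 = 101.5, so 102 analysed; 102/0.7 gives 146 recruited.
- ICC 0.05: 2.35 × 49.06 = 115.3, so 116 analysed; 116/0.7 gives 166 recruited.

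**The case against.** The strongest objection is that the harm depends on an ICC that the article never gives and that could be close to zero. Several features would keep it low: half the sessions are individual, each patient follows an individualised programme, trainers work to a standardised protocol, HRSD raters are blinded and trained for agreement, and patients who leave the exercise stay in the intention-to-treat analysis. All of this stands as a limit on size. None of it removes correlation arising from shared sessions.

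A reader might infer that patients stay in one closed group with one trainer for six months. The article does not say so. Inclusion runs for 18 months, so membership may roll, and a fixed m is a simplification.

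Analysing without location, after randomising within location, tends to overstate the standard error when locations differ in outcome. That could offset some of the clustering effect, and the article does not settle the net result. It is a reason to put location in the model, not to leave the group out.

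Finally, an analysis plan that is not shown may add model terms, and the phrase analysis of variance does not strictly exclude nested factors. That weakens the analysis half of the point. It does not help the Sample size section, whose calculation is complete as stated and has no allowance.

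**Conclusion.** The point holds conditionally. The documents establish group delivery in one arm only, a sample size equal to the independent-observations result with no reserve, and a named analysis with no stated group term. If within-group correlation is positive, the standard error of the HRSD difference is too small, other things equal, and the stated 80% power is too high.

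The size rests on assumptions. With groups of 8, 100 analysed per arm and ICC between 0.01 and 0.05, type I error of the planned test is about 5.4% to 7.1%, and power of a test allowing for clustering is about 79% to 74%. At the lower end this is negligible.

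Two stronger readings are not supported. One is that the standard errors are too small as a matter of fact: no ICC is given, so this cannot be shown. The other is that the planned test combines a 7.1% type I error with 74% power: those figures describe two different tests. ICCs or groups larger than those used here would give worse figures, but nothing in the article points to them.

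The plan should be changed because the remedy is cheap and the sample size leaves no margin. The point does not undermine the design.

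**What to change.** 1. Record the exercise group and instructor of each exercise-arm patient. If groups are open and rolling, record instructor or location by period as the clustering unit. Instructors already register compliance during training sessions (Table 1), so this adds little work.
2. Analyse HRSD with a partially nested mixed model: a random group effect in the exercise arm only, controls as singletons, location as a factor, and small-sample degrees of freedom.
3. State the expected group size, and restate the power at the planned 140 recruited per arm over ICC 0.01 to 0.05.

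The cost is one or two recorded variables and a different model statement. The confidence interval may be wider and the stated power somewhat lower. Treatment delivery does not change.

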### Compliance and withdrawal

In order to improve compliance during the intervention period, a protocol will be followed concerning missed exercise therapy sessions by participants. This protocol includes: 1) active approach by the exercise instructor in case of no show, and 2) encouragement of other participants to contact each other in case of no show. Participants can withdraw at any time for any reason without any consequences. Also, the investigator can decide to withdraw a participant from the study for urgent medical reasons. Participants who withdraw from the intervention will be asked the reason(s) for drop-out but will be retained in the study for the intention to treat analysis.

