### Randomisation, blinding and treatment allocation

Randomisation takes place at every location separately. This way, every location will have an equal distribution of participants between the intervention and control group. The SPSS random generator (SPSS version 14.0) [50] will be used to allocate patients. Ten closed envelopes with allocation numbers are presented to the participants. They choose an envelope, after which the research assistant tells the patients in which arm of the study they are included. Evaluators of the main outcome measure (HRSD) are blinded for group allocation and are trained regularly for inter-rater reliability. All other measures will be evaluated by a research assistant, who is not blinded for group allocation.

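### Withdrawal for urgent medical reasons is worded as leaving the study, which, read literally, ends primary-outcome follow-up and does not fit the intention-to-treat commitment

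*Protocol article*

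**What the plan says.** The paragraph on Compliance and withdrawal in the protocol article covers three situations.

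- The participant's own decision: "Participants can withdraw at any time for any reason without any consequences".
- The investigator's decision: "Also, the investigator can decide to withdraw a participant from the study for urgent medical reasons".
- Stopping the exercise: "Participants who withdraw from the intervention will be asked the reason(s) for drop-out but will be retained in the study for the intention to treat".

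Under Statistical analyses the commitment carries no exception: "The primary analysis of the data set will be according to the 'intention to treat' principle". The Discussion lists intention to treat among the features that make this a high-quality trial. The Background names its absence as a weakness of earlier trials.

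Table 1 schedules the HRSD at T0, T3, T6 and T12, as a 20-minute interview by a blinded rater.

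**The concern.** The paragraph separates leaving the study from leaving the intervention, and promises retention only for the second. A participant whom the investigator takes out of the study is, in ordinary usage, no longer in it, so the remaining HRSD interviews would not be held. Yet the HRSD is an interview and does not depend on whether the patient is exercising. Nothing in the article explains why an urgent medical reason should in general end measurement as well as exercise.

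The missing values would not be a random sample. An urgent medical problem may well go with a different course of depression, so the loss could be related to the outcome itself. An analysis plan can say how missing values are handled, but it cannot recover interviews that were never attempted. This is a rule of trial conduct, and the article states it.

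**Working it through.** **1. The sentences side by side.**

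| Event | Leaves what | Retention stated? |
|---|---|---|
| Participant withdraws | not specified | no |
| Investigator withdraws the participant, urgent medical reasons | the study | no |
| Participant withdraws from the intervention | the intervention | yes, for intention to treat |

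Both rules can be followed at once. Followed literally, they leave the second row without outcome follow-up.

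**2. The plan's own sample size.** Inputs from Sample size: "Adding exercise to usual care is expected to result in a decline of at least eight points in HRSD score (thus two extra points"), and "with an α (two-tailed) of 5% and a power (1-β) of 80%, using two equal groups and a standard deviation of 5 points, 100 patients" per group.

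- n per group = 2 × (1.96 + 0.842)² × 5² / 2² = 2 × 7.85 × 6.25 ≈ 98.1, so 99. The stated 100 is reproduced.
- With 140 included and 30% lost, 140 × 0.70 = 98 remain, and power is 80.0%.
- If medical withdrawals came on top of the 30%, an assumed extra 1%, 2% or 5% would give power of 79.4%, 78.8% or 77.0%. If they fall within the 30%, power is unchanged.

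Power is therefore not the issue. The drop-out allowance protects numbers, not against selective loss.

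**3. Possible bias.** The article gives no rate of medical withdrawal, so f below is an assumption. Let f be the fraction of an arm removed and d the mean HRSD improvement those patients would have had. Suppose the retained patients improve by the planned 8 points (exercise) and 6 points (control), and only observed patients are analysed.

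- True exercise mean = (1 − f) × 8 + f × d, so the observed mean is too high by f(8 − d).
- By the same step, the observed control mean is too high by f(6 − d).
- Equal f and equal d in both arms: net bias = f(8 − d) − f(6 − d) = 2f, whatever d is.
- Removals only in the exercise arm, d = 0: bias = 8f in favour of exercise.
- Removals only in the control arm, d = 0: bias = 6f against exercise.

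| f | patients of 140 | equal in both arms (2f) | exercise arm only, d = 0 (8f) | control arm only, d = 0 (6f) |
|---|---|---|---|---|
| 2% | about 3 | 0.04 | 0.16 | −0.12 |
| 5% | 7 | 0.10 | 0.40 | −0.30 |
| 10% | 14 | 0.20 | 0.80 | −0.60 |

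As a share of the planned 2 points, equal removal gives 2% to 10% and the exercise-only extreme gives 8% to 40%. If the exercise-only patients would have improved by 6 points, as under usual care, the bias is f(8 − 6) = 2f again.

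**The case against.** The strongest reply is that nothing in the article says HRSD interviews stop, that collected data are discarded, or that these patients leave the analysis set. The provision is discretionary and limited to urgent medical reasons. The article condenses a fuller protocol that may settle the matter. On this view the point is a request for clarity. Part of that stands: the loss of follow-up is the natural reading of the sentence, not something it spells out. But the wording is in the article, retention is promised for one kind of withdrawal only, and the same correction is right whether the phrase is literal or a slip.

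A reader might infer more than the document supports:

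- **That the two sentences contradict each other.** They do not. They concern different events, and the retention rule covers only withdrawal from the intervention, not other withdrawals generally.
- **That only the exercise arm is affected.** The sentence applies to any participant. Controls include inpatients, are advised to exercise regularly and do the same cycling test. A medical reason to stop the supervised programme can arise only in the exercise arm, so an imbalance is plausible, but it is not established.
- **That the decision is made with the arm known.** The relevant sentence is "All other measures will be evaluated by a research assistant, who is not blinded for group allocation". It concerns who evaluates the secondary measures. The article does not say who decides on withdrawal or whether that person knows the allocation.
- **That safety follow-up is cut off.** The article describes no safety follow-up schedule that this sentence would shorten.
- **That the analysis is then not intention to treat.** Some missing outcomes do not by themselves make it so. The risk is bias from informative missingness.

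**Conclusion.** The point holds as a weakness of wording with a real but unquantified consequence. Read literally, participants withdrawn for urgent medical reasons lose their remaining primary-outcome assessments, and this does not fit an intention-to-treat commitment made without exception. It is worth correcting, but it is not a contradiction and not evidence of a bias towards exercise.

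Neither the size nor the direction of any bias can be read from the article. The range of 0.04 to 0.20 HRSD point rests on assumed rates of 2% to 10%, equal removal and equal prognosis of removed patients in both arms, and a complete-case analysis. The range of 0.16 to 0.80 point also needs every removal to be in the exercise arm and no improvement in any of those patients, so it is an upper extreme. If removals fell mainly among controls, the bias could run the other way. The eligibility criteria already exclude significant cardiovascular disease and joint or hip pathology, which makes the higher rates less likely.

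**What to change.** Reword the sentence so that withdrawal for urgent medical reasons is from the intervention, with the participant retained in the study. State that the remaining HRSD interviews and questionnaires are attempted where the participant consents and assessment is medically feasible. Record the reason and date of each such withdrawal by arm, so that any imbalance can be seen. Decisions about stopping exercise, and about whether an assessment is suitable for a given patient, stay with the clinicians. The change does not require participation to continue in every case short of withdrawn consent.

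The cost is one sentence and a few extra interviews and questionnaires at visits already planned. Some of these patients will be hard to reach, so the change reduces the missing data without removing it.

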### Statistical analyses

Comparability of the intervention and control groups will be examined for the baseline measurements. If necessary, analyses will be adjusted for baseline differences. The primary analysis of the data set will be according to the 'intention to treat' principle. A secondary 'per protocol' analysis will be done taking into account the level of compliance and the amount of exercise during the intervention period. Usual daily physical activity, tobacco smoking and alcohol intake will be treated as confounders.

Differences in remission rates (and other categorical outcomes) between the experimental groups are examined by contingency table Chi-square statistics. Differences in mean scores on continuous outcomes (e.g. HRSD) between the intervention groups are examined by analysis-of-variance.

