### Summarized aims and hypothesis of EFFORT-D

The main objective of the study is to assess the effectiveness of exercise therapy (running therapy (RT) or Nordic walking (NW)), in addition to usual care, on depression in adult patients. We hypothesize that adding exercise therapy to usual care will result in a larger reduction in depressive symptoms (as measured with the Hamilton Rating Scale of Depression, (HRSD)) during a 6 month treatment program as well as at 6 months follow-up, compared to usual care without exercise therapy.

Secondary aims are to assess the effectiveness of exercise therapy (RT or NW) on the following outcome measures: 1) Cardiovascular and metabolic risk parameters as fitness (VO2 max, grip strength), BMI, waist circumference, body composition, blood pressure, fasting blood glucose, cholesterol HDL/LDL ratio and CRP, 2) Co-morbid symptoms of anxiety and pain 3) Quality of life, and 4) Cost-effectiveness.

To assess whether there are subgroups of patients who show a larger or less effect of exercise therapy on depression, subgroup analysis will be conducted differentiated on demographic variables (age, sex) and level and type of depression based on the HRSD, personality traits and level of fitness.

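### Baseline adjustment of the HRSD comparison is left conditional with no rule, which costs precision, and no primary visit is named although the sample size covers one 5% test and the hypothesis two periods

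*Protocol article*

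**What the plan says.** All references are to the protocol article.

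- **Statistical analyses.** The groups are first examined for comparability at baseline, then: "If necessary, analyses will be adjusted for baseline differences". For the outcome itself: "Differences in mean scores on continuous outcomes (e.g. HRSD) between the intervention groups are examined by analysis-of-variance". The section names physical activity, smoking and alcohol as confounders. It does not name baseline HRSD.
- **Summarized aims and hypothesis of EFFORT-D.** A larger reduction in HRSD is expected "during a 6 month treatment program as well as at 6 months follow-up".
- **Sample size.** The expected reductions are 6 points under usual care and 8 with exercise, tested "with an α (two-tailed) of 5% and a power (1-β) of 80%, using two equal groups and a standard deviation of 5 points". The result: "100 patients are needed in each group". Then: "Taking 30% drop-out into account, 140 patients have to be included in each group". The text does not say whether the 5 points are the SD of the change or of the follow-up score, and it names no visit.
- **Table 1.** HRSD is rated by a blinded rater at T0, T3, T6 and T12.
- **Randomisation, blinding and treatment allocation.** "Randomisation takes place at every location separately".
- **Discussion.** A one-tailed analysis is kept open in case recruitment falls short.

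**The concern.** Two features of the primary comparison are left open.

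The first is the model. Whether baseline is adjusted for depends on the observed baseline differences, with no criterion. The value of adjusting for baseline HRSD does not come from imbalance. It comes from the correlation between baseline and later HRSD, which is present whether or not the arms happen to differ. A rule that adjusts only when they differ gives up most of that gain and leaves the choice to the analyst.

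The second is the time point. The abstract's primary outcome, the hypothesis, the sample size and the analysis section name no single primary visit, and the hypothesis spans two periods. A sample size for one 5% test then matches neither reading of success. If a result in either period counts, the 5% is not kept. If both are needed, the 80% is not delivered.

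**Working it through.** **Inputs from the document:** difference 2 points (8 minus 6), SD 5, two-sided α 0.05, power 0.80, equal groups, 30% drop-out.
**Assumed, because the document gives none:** baseline to follow-up correlation ρ of HRSD 0.3-0.7, and correlation r between the T6 and T12 test statistics 0-0.9.

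**1. The plan's own figure.** n per group = 2 × [5 × (1.960 + 0.842) / 2]² = 98.1, so 99. The exact t calculation gives 100, as stated. For drop-out, 100 / 0.7 = 143 against the stated 140; conversely 140 × 0.7 = 98 evaluable, with power 79.6%. The 100 and 140 reproduce closely enough, and the calculation uses no baseline adjustment.

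**2. Always adjusting for baseline HRSD, 100 per arm.** The residual SD of ANCOVA is 5√(1 − ρ²) if 5 is the SD of the follow-up score. It is 5√((1 + ρ)/2) if 5 is the SD of the change, taking equal SDs at baseline and follow-up. Power is Φ(2 / (SD × √(2/100)) − 1.960). With SD 5 this is Φ(2.828 − 1.960) = 80.7%.

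| ρ | Adjusted SD (5 = follow-up SD) | Power | Adjusted SD (5 = change SD) | Power |
|---|---|---|---|---|
| 0.3 | 4.77 | 84% | 4.03 | 94% |
| 0.5 | 4.33 | 90% | 4.33 | 90% |
| 0.7 | 3.57 | 98% | 4.61 | 87% |

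Put as sample size, 80% power would need 90, 74 or 51 per group on the first reading, and 64, 74 or 84 on the second.

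**3. Adjusting only if baseline differs.** This was simulated with 60,000 trials and 100 per arm, on the follow-up-score reading. ANCOVA was used if the baseline difference had p < 0.05, and otherwise an unadjusted comparison.

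| ρ | Type I error, conditional rule | Power, conditional rule | Power, always ANCOVA |
|---|---|---|---|
| 0.3 | 4.8% | 81% | 84% |
| 0.5 | 4.3% | 81% | 90% |
| 0.7 | 3.7% | 82% | 98% |

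The conditional rule is conservative and recovers little of the precision.

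**4. No primary visit, taking T6 and T12 as the two time points.**

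- *Either suffices, each tested at 5%.* With independent tests the error rate is 1 − 0.95² = 9.8%. By simulation of correlated tests it is 9.1% at r = 0.5, 8.3% at r = 0.7 and 7.1% at r = 0.9.
- *Both must succeed.* The error rate stays at or below 5%. With a true 2-point difference at both visits and 100 evaluable per arm, power is 0.807² = 65% if independent, 70% at r = 0.5 and 72% at r = 0.7.

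**The case against.** The plan can be defended as valid. The stated 100 per group gives 80% power without adjustment, so nothing promised is lost by leaving baseline out, provided the quantity analysed is the one to which the SD of 5 belongs. The primary outcome is a reduction in HRSD, so the analysis of variance may be of change, which already uses each patient's baseline. Both points stand. They do not remove the gain, because ANCOVA is more precise than either unadjusted analysis at every correlation assumed. The size of the gain does rest on those assumptions.

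A reader might go further in four ways that the document does not support.

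- *The conditional adjustment inflates the error rate.* A fixed rule does the opposite (3.7-4.8%). Choosing among follow-up ANOVA, change ANOVA and ANCOVA after seeing results could reach 9-10%, but the text ties adjustment to baseline comparability, not to results.
- *Three separate tests give 8-14% error.* T3, T6 and T12 are measurement times. The article states no test per visit, and a repeated-measures analysis of variance is not excluded.
- *The plan suffers both inflated error and lost power.* The two belong to opposite readings of the hypothesis and cannot hold together.
- *Leaving out location is an error.* The article is silent on location in the model, and such terms are commonly left to the full protocol or SAP. No between-location variance is given, so a cost cannot be computed.

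**Conclusion.** The point holds on two counts, both moderate.

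Conditional adjustment without a rule forgoes precision that is available free. Power would be about 84-98% (SD 5 as follow-up SD) or 94-87% (SD 5 as SD of change) instead of about 80%, at 100 per arm, a 2-point difference and ρ rising from 0.3 to 0.7.

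The single 5% test behind the sample size is not tied to a visit, while the hypothesis covers two periods. The consequence is either an error rate of about 7-10% (r from 0.9 down to 0) or a power of about 65-72% (r from 0 to 0.7), depending on which reading the investigators intend.

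The stated sample size is arithmetically sound. That the two gaps exist is certain from the text. The figures depend on correlations that the document does not give.

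**What to change.** Replace the conditional sentence with one pre-specified primary analysis: a two-sided 5% comparison of HRSD at a single named visit, for example T6 as the end of the intervention. Use ANCOVA, or the same contrast from a mixed model, and always include baseline HRSD. Stating two-sided here also settles the one-tailed option left open in the Discussion. Treat the other visits as secondary, or test them in a fixed order after the primary one. State in the sample size section which visit it refers to and whether the SD of 5 is of the change or of the score.

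The cost is wording only, since every variable is already collected and 100 per group still suffices. The small downside is that T12 becomes secondary or conditional on the primary visit. If the investigators prefer to keep two tests in parallel, a Bonferroni split at 100 per group leaves 72% power for each unadjusted test, so a fixed order is cheaper.

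As an option, location could be added as a covariate because randomisation is done within it. This is a suggestion, not a correction.
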